
### 2.2. Experimental Vignettes

The four vignettes describe distinct configurations of AI involvement in facial reconstructive surgical planning, varying both the AI’s task (imaging analysis, decision support, outcome simulation, autonomous planning) and the surgeon’s level of supervision (Table 1). Each configuration corresponds to a capability documented in the current literature: anatomical structure analysis from CT [6,8], algorithmic generation of candidate surgical plans [9], three-dimensional simulation of postoperative facial appearance [12,13], and highly autonomous planning of the kind anticipated by surgical-autonomy frameworks [14,15]. All vignettes open with an identical premise (the respondent needs facial reconstructive surgery following an injury) and are written in parallel second-person wording of comparable length and reading difficulty, so that scenario content—not framing—drives differences in responses. Because the four configurations differ in what the AI does as well as in how much the surgeon decides, a perceived difference between them could in principle reflect technical sophistication rather than autonomy. Three features are intended to keep the two apart. First, every vignette closes by stating explicitly how the final surgical plan is reached and by whom. In Scenarios A–C, a single clause of parallel construction names the surgeon as the decision-maker (making all decisions, choosing among the proposed options, or deciding the final plan after reviewing the simulations); in Scenario D, the closing sentences state that the surgeon reviews the AI’s plan but rarely modifies it. What varies is therefore the decisional locus, not the computational task. Each comprehension check is built on that same feature: the decision-maker in Scenarios A and B; the role of the system in Scenario C (whose decisional clause is functionally equivalent to Scenario B’s, so that the role is what distinguishes the two); and the origin of the plan actually followed in Scenario D. Second, the vignettes are matched on the quantity of technical detail supplied—one sentence describing the system’s input and output in each case—so that described sophistication does not rise in step with autonomy. Scenario C specifies a generative three-dimensional simulation, computationally the most elaborate output in the set, yet leaves the decision entirely with the surgeon; Scenario D describes a comparatively conventional optimization whose distinguishing feature is decisional rather than technical. Third, two manipulation checks follow every scenario: MAN1, perceived control of the AI over the final decision, and MAN2, perceived technical sophistication of the system. The manipulation is treated as valid only if MAN1 orders the scenarios as intended; MAN2 verifies that sophistication does not itself increase monotonically with autonomy and enters a pre-specified sensitivity analysis as a covariate, so that the autonomy effect can be estimated with perceived sophistication held constant (Section 2.9.1). The full vignette texts are provided in Appendix A.

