
### 2.8. Pilot Study and Instrument Validation

The instrument will be validated in a pilot study (*N* = 50, not included in the main sample, allocated 1:1 to the ascending sequence A → B → C → D and to its exact reverse D → C → B → A) before the main study is launched. The pilot will estimate (i) internal consistency—Cronbach’s α and McDonald’s ω with 95% confidence intervals for each three-item composite, computed separately per scenario, against a threshold of ≥0.70, with ω reported alongside α in line with current psychometric guidance [73]; with three items per construct, α ≥ 0.70 requires a mean inter-item correlation of only $\bar{r}$ ≥ 0.44 under the generalized Spearman–Brown relation (Figure 2), a realistic requirement for parallel items; (ii) inter-item correlations (flagged at r > 0.90 for redundancy or r < 0.20 for heterogeneity) and corrected item-total correlations (threshold ≥ 0.40), plus the correlation between repeated measurements, reported with a 95% confidence interval, to verify the ρ ≈ 0.50 planning assumption and, where it is not met, to trigger the adaptive sample-size rule of Section 2.5; (iii) the factor structure of the nine response items, via exploratory factor analysis (principal-axis extraction, oblique rotation, sampling adequacy KMO ≥ 0.70, Bartlett’s test of sphericity, parallel analysis as the retention criterion)—an anticipated risk is that acceptability and trust items form a single factor, in which case the two constructs will be merged into a single “trust–acceptance” score and the analysis plan adjusted transparently before pre-registration, with this decision taken exclusively on pilot data; (iv) first-attempt comprehension-check pass rates per scenario (threshold ≥ 70%); (v) manipulation validity—MAN1 scores must order the scenarios from A to D in both pilot arms, while MAN2 (perceived technical sophistication) must not increase monotonically with autonomy; if it does, the vignettes will be reworded to equalize the described sophistication of the systems and the check repeated before pre-registration; (vi) fatigue—perceived difficulty (DIF1) and section-wise drop-out across serial positions in both arms; (vii) cognitive interviews with 5–8 participants to identify confusing wording, probing in particular whether RES1–RES6 are read in the intended senses of moral answerability, outcome-independent accountability, and legal fault (Section 2.6); and (viii) a first bound on order effects—the two pilot arms are compared on the three composites and on MAN1 by a scenario × order mixed ANOVA (*n* = 25 per arm; minimum detectable interaction *f* = 0.17 at ρ = 0.50), which can exclude medium-to-large order artifacts but not small ones, the definitive test being the main-study interaction. The four-sequence randomizer used in the main study is implemented in the same pilot build. Because the pilot itself exercises only two of the four arms, the randomizer is verified there by simulated allocation, which also confirms that the allocated sequence and the serial position of each scenario are stored correctly. A ninth objective is included: (ix) the keying and dimensionality of the four general-attitude items (G1–G4), since G3 is a caution item that the present scoring treats as positively keyed while G2 and G4 are reversed; the scoring rule for that block is fixed on pilot data before pre-registration, and if the four items do not form a single interpretable dimension they will enter the person-level analyses individually rather than as a composite. Because a sample of 50 is at the lower limit for stable factor solutions, the pilot EFA is treated as provisional: the factor structure will be re-examined by confirmatory factor analysis on the main sample (*N* = 300), with acceptable fit defined a priori as CFI/TLI ≥ 0.95, RMSEA ≤ 0.06, and SRMR ≤ 0.08. Because the same nine items are answered four times, longitudinal measurement invariance across the four scenario repetitions (configural, metric, and scalar) will also be tested on the main sample; at least partial scalar invariance is required for the between-scenario comparison of composite means, and any non-invariant item will be reported and handled by partial-invariance modeling. Pilot results will be reported in the methods section of the results article.

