Trust in the healthcare system	B6	Likert 1–7	Covariate/exploratory moderator
Manipulation check (technical sophistication)	MAN2, per scenario (×4)	Likert 1–7	Design validation/covariate
Presentation sequence	SEQ	4 categories	Between-subjects design factor
Serial position of scenario	POS	1–4	Covariate (order, fatigue)

Abbreviations: DV, dependent variable; ACC, acceptability items; TRU, trust items; RSK, perceived-risk items; RES, responsibility items; MAN1 and MAN2, manipulation-check items; DIF1, perceived-difficulty item; ATT1 and ATT2, attention checks; CC_A–CC_D, comprehension checks; B1–B6, background items; G1–G4, general-attitude items; P1–P4b, preference items; D1–D7, demographic items; SEQ, presentation sequence; POS, serial position of the scenario; H1–H4, hypotheses 1–4.

**Table 5 healthcare-14-03030-t005:** Hypothesis-by-hypothesis analysis plan.

Hypothesis/Objective	Planned Test	Reported Coefficients
Manipulation validation	Mixed RM-ANOVA on MAN1 (autonomy within × sequence between) + polynomial trend contrasts; the intended ordering A → D expected within every sequence	*F*, corrected *df*, *p*, partial η^2^; ε(GG)
H1. acceptability and trust decline with autonomy	Mixed RM-ANOVA per composite, sequence as between-subjects factor (Greenhouse–Geisser) + orthogonal polynomial trend contrasts (linear, quadratic, cubic); post hoc dependent *t*-tests, Holm correction	*F*, corrected *df*, *p*, partial η^2^ (90% CI); pairwise dz (95% CI)
H2. perceived risk increases with autonomy	Mixed RM-ANOVA (autonomy within × sequence between) + orthogonal polynomial trend contrasts; post hoc dependent *t*-tests, Holm correction	*F*, corrected *df*, *p*, partial η^2^; pairwise *dz*
H3. responsibility migrates surgeon → AI developer	4 × 4 mixed ANOVA (scenario × actor within, sequence between), Greenhouse–Geisser; the scenario × actor interaction is the test of H3; repeated with a serial-position term	*F*, corrected *df*, *p*, partial η^2^; ε(GG)
Responsibility concentration	Normalized Herfindahl–Hirschman index (RES1–RES3) per scenario, compared by mixed RM-ANOVA (sequence between)	Mean HHI per scenario; *F*, *p*, partial η^2^
Moral–legal distinction	Mixed RM-ANOVAs on RES5 and RES6 across scenarios (sequence between); Holm correction within family	*F*, corrected *df*, adjusted *p*, partial η^2^

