H4. moderation by AI familiarity (partially exploratory)	RM-ANCOVA or linear mixed model with random intercepts: scenario (within) × B1 (centered), sequence between	F (or likelihood-ratio test), *p*, *f*^2^; simple slopes with 95% CI
Global preference (P1)	Goodness-of-fit chi-square over 6 analysis categories (2 undecided options pooled); standardized residuals; consistency with maximum-acceptability scenario, descriptive	χ^2^, *df*, *p*, *w*; standardized residuals
Predictors of acceptability	Person-level multiple regression: mean acceptability on familiarity, general attitudes, demographics	*B*, *SE*, β, 95% CI, R^2^, VIF
P2, P4a/P4b (exploratory)	Brief thematic analysis (P2); descriptive statistics, within-person P4a–P4b difference, and correlations with RES5/RES6	Theme frequencies; Pearson/Spearman *r*
Order dependence (design validation)	Scenario × sequence interaction in the mixed RM-ANOVA; position-adjusted linear mixed model (autonomy + serial position, random intercepts)	*F*, corrected *df*, *p*, partial η^2^ (90% CI); adjusted vs. unadjusted scenario means
Functional form of the autonomy effect	Orthogonal polynomial contrasts (linear, quadratic, cubic); Holm-corrected adjacent-pair contrasts	*F*, *p*, partial η^2^ per contrast; share of the omnibus effect
Autonomy vs. technical complexity	Mixed RM-ANOVA on MAN2 (sequence between); primary models re-estimated with MAN2 as a time-varying covariate	*F*, corrected *df*, *p*, partial η^2^; adjusted scenario means
Between-person heterogeneity (exploratory)	Random-slope linear mixed model; latent-class growth analysis of individual trajectories	Likelihood-ratio χ^2^, *p*; random-slope SD; class sizes, BIC, entropy

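### Section 2.2 calls the decision-making in Scenarios B and C equivalent, yet the pilot validity rule needs MAN1 to rise from B to C and B–C is a candidate autonomy break

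*Protocol article*

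**What the plan says.** Section 2.2 (Experimental Vignettes) defines the manipulated quantity: "What varies is therefore the decisional locus, not the computational task". In explaining the comprehension checks, it then describes Scenario C as one "whose decisional clause is functionally equivalent to Scenario" B's, and adds that the AI's role is what tells the two apart. It also describes C's simulation as "computationally the most elaborate output in the set, yet leaves the decision entirely with the surgeon". In Table 1 the AI proposes three plans in B, and in C it simulates the postoperative appearance for each option.

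The first manipulation check is "MAN1, perceived control of the AI over the final decision". Section 2.2 sets the rule: "The manipulation is treated as valid only if MAN1 orders the scenarios as intended". Section 2.8(v) makes it concrete for the pilot: "MAN1 scores must order the scenarios from A to D in both pilot arms". For the main study, Table 5 words it as an expectation: "the intended ordering A → D expected within every sequence". No section provides for a tie between B and C.

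For the outcomes, Table 5 analyses functional form by "Orthogonal polynomial contrasts (linear, quadratic, cubic); Holm-corrected adjacent-pair contrasts". Section 2.9.1 states that a break is located only from the adjacent pairs A–B, B–C and C–D.

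**The concern.** If decision-making is equivalent in B and C, a respondent who reads the vignettes as Section 2.2 describes them has no decisional reason to rate AI control higher in C. Table 1 could even suggest the reverse, because the AI proposes plans in B and only simulates appearance in C. The pilot rule nevertheless needs C to score above B, twice. A manipulation that works exactly as described can therefore fail its own validity check, and the B–C part of the result is then decided by sampling error.

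The same conflict reaches interpretation. If acceptance differs between B and C, the plan would place an autonomy break there, although by its own account only the AI's task has changed. If acceptance is flat from B to C because control is flat, the polynomial decomposition shows a departure from a straight line that could be taken for a threshold in autonomy. Whether the decline is a gradient or a step is one of the study's headline questions.

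**Working it through.** **The plan's own figures.** The protocol gives no probability of meeting the MAN1 rule, so there is none to reproduce. Its sample-size figures do reproduce. With λ = N·m·f²/(1−ρ), m = 4, f = 0.10 and ρ = 0.50, power 0.80 is reached at N = 138, where λ = 138·4·0.01/0.50 = 11.04 on 3 and 411 df. The detectable dz at N = 300 and α = 0.05/6 comes out at 0.203, against the stated 0.20. None of these is in dispute.

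**Inputs.** From the protocol: two pilot arms of 25, four main-study sequences of 300/4 = 75, and ρ = 0.50. Assumed: independent arms, A and D far enough from B and C that only the B–C order is uncertain, and ρ = 0.50 for MAN1 as well.

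**Chance of the required order.** In SD units, the within-person C−B difference has SD √(2(1−ρ)) = 1. In an arm of size n the mean difference has standard error 1/√n. For a true gap δ, C exceeds B in one arm with probability Φ(δ√n), and in all k arms with probability Φ(δ√n)^k.

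| True gap C−B (SD) | Pilot, n = 25, k = 2 | Main study, n = 75, k = 4 |
|---|---|---|
| 0 | 0.5² = 0.25 | 0.5⁴ = 0.06 |
| 0.1 | Φ(0.50)² = 0.48 | Φ(0.87)⁴ = 0.42 |
| 0.2 | Φ(1.00)² = 0.71 | Φ(1.73)⁴ = 0.84 |
| 0.3 | Φ(1.50)² = 0.87 | Φ(2.60)⁴ = 0.98 |

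The first row does not depend on the SD or on ρ. A simulation with 7-point rounding (assumed SD 1.5) and equal B and C gave 0.22 in the pilot for a strict order and 0.28 with tied means allowed. For the four sequences it gave 0.05 and 0.07. If C is perceived 0.3 scale points below B, the pilot figure falls to 0.02–0.04. With true steps of one point each it is 0.99.

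**Polynomial shares.** The coefficients are not printed, so conventional equal spacing is assumed: (−3, −1, 1, 3), (1, −1, −1, 1), (−1, 3, −3, 1). Each sum of squares is (c·μ)²/(c·c).

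- Profile (0, 1, 1, 2): linear 6²/20 = 1.80; quadratic 0²/4 = 0; cubic 2²/20 = 0.20. Shares are 90%, 0% and 10%.
- Profile (0, 1, 1, 3): linear 9²/20 = 4.05; quadratic 1²/4 = 0.25; cubic 3²/20 = 0.45. Shares are 85.3%, 5.3% and 9.5%.
- Profile (0, 1, 2, 3): 100% linear.

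For (0, 1, 1, 2) at N = 300, ρ = 0.50 and f = 0.25, the centred profile is 0.354·(−1, 0, 0, 1). The cubic noncentrality is then 0.707·√300/√(20·0.50) = 3.87, which gives power 0.97. At f = 0.10 it is 1.55, with power 0.34.

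**The case against.** The equivalence remark sits in a parenthesis about why C's comprehension check targets the AI's role. It concerns one closing clause, not autonomy as a whole, and Section 2.2 opens by saying that both task and supervision vary. The vignettes and the MAN1 item are not shown, and MAN1 is a graded perception, so naming the same decision-maker does not force equal means. With a modest real gap of 0.2–0.3 SD, the pilot rule is met about 0.71–0.87 of the time. The pilot precedes pre-registration, and Section 2.12 counts vignette rewording among pilot-based decisions, so a B–C tie would serve as an early warning. All of this stands. It limits the size of the problem but does not reconcile the passages.

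A reader might go further in three ways that the document does not support.

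- **A main-study gate.** A reader might infer that a failed order in any of the four sequences invalidates the main study. Section 3 and Table 5 word that order as expected, and the planned test is a mixed ANOVA on MAN1 with trend contrasts. The 0.06 is the chance of seeing the expected pattern, not of passing a rule.
- **A settled three-tier scale.** A reader might infer that A, {B, C}, D is the plan's own gradient. Scenarios A, B and C all name the surgeon as decision-maker, so the text does not secure A below C either. Only the B–C equivalence is stated outright.
- **Invalid tests of H1 and H2.** A reader might infer that the confirmatory tests are distorted. The omnibus, pairwise and equivalence tests need no level spacing, and a flat B–C step would show in them. Section 2.9.1 says the polynomials cannot locate a break and sets no cutoff for a substantial cubic share, so a 10% share need not be called a departure.

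**Conclusion.** The point holds as an inconsistency to fix before the pilot. A stated validity rule conflicts with the plan's own description of the manipulation, and B–C is offered as a possible autonomy break although the plan says that only the AI's role differs there. If B and C are perceived as equal in control, the pilot rule is met about 1 time in 4, and the pattern expected in all four main sequences appears about 1 time in 16. Equality is an assumption. The 1-in-4 and 1-in-16 figures also need independent arms and well-separated A and D; the figures for non-zero gaps further need ρ = 0.5. The 10% cubic share rests on equal spacing and affects only the reading of functional form. SHOULD-FIX.

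**What to change.** Reconcile Sections 2.2, 2.8(v), 2.9.1 and Table 5 before the pilot, in one of two ways.

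1. State what makes C higher in AI control than B, and withdraw the equivalence statement. The A-to-D rule can then stay.
2. Keep the equivalence statement, and restate the MAN1 criterion as A below both B and C, and both below D, with B–C unordered and reported with the equivalence test at the dz = 0.20 bound already fixed. That test is informative at N = 300, where the 90% interval half-width is about 1.65/√300 = 0.10. It cannot succeed on the 50 pilot respondents (1.68/√50 = 0.24, wider than the bound), so an interval is enough there.

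Under the second option, interpret a B–C difference as a change of AI task at an equivalent decisional locus, and do not read a cubic component that comes from a flat B–C step as a threshold in autonomy. The contrasts A vs mean(B, C) and mean(B, C) vs D may be added as supporting analyses. Replacing the confirmatory trend contrasts, or spacing them at pilot MAN1 means, is not needed. Spacing from 50 respondents would carry pilot noise into the tests of H1 and H2.

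The cost is rewording, with no change to sample size or data collection. The second option gives up the claim of four strictly ordered autonomy levels, and in return B–C becomes a built-in comparison of task at an equivalent decisional locus. Relaxing the rule only after a failed pilot check would look driven by the result.

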
### 2.3. Participants: Eligibility Criteria

Inclusion criteria: age ≥ 18 years; current residence in Romania; ability to read and complete an online questionnaire in Romanian; and informed consent expressed by ticking the consent checkbox on the first page of the instrument. Exclusion criteria applied at screening: age < 18 years, residence outside Romania, or refusal of consent. Exclusion criteria were applied at data cleaning, following current recommendations for careless-responding control [68,69]: failure of both embedded attention checks; incorrect response to the comprehension check—after re-presentation of the scenario (second attempt)—for at least two of the four scenarios; invariant response patterns (the same response selected for every Likert-type item in the questionnaire); and duplicate records (identical response patterns across all variables, submitted consecutively).

### 2.4. Recruitment and Setting

Participants will be recruited online through social networks, forums, and professional groups in Romania, and through the mailing lists of higher-education institutions, with the approval of the respective administrations. No financial compensation is offered; participation is entirely voluntary, and participants are informed that they can stop at any time. The resulting sample is a non-random convenience sample. The study makes no claim of national representativeness: the demographic structure of the sample (including residence environment and development region) will be reported against reference data from the Romanian National Institute of Statistics, and generalizability will be discussed explicitly as a limitation. The validity of between-scenario comparisons—the study’s primary objective—is protected by the within-subjects design, in which every participant evaluates all four scenarios, so that comparisons across autonomy levels do not depend on sample composition or recruitment method. Feasibility is supported by comparable online surveys of attitudes toward AI in healthcare, which recruited samples of approximately 200–2700 respondents from online populations [24,27,34].

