### 1.2. Public Attitudes Toward Medical AI

A substantial body of the recent literature has characterized public and patient attitudes toward clinical AI. Syntheses converge on a consistent pattern: the public is broadly receptive to AI as a support tool but insists on human involvement and personalized care [21,22]. Large surveys find that most patients expect AI to improve care while reporting substantial concerns about misdiagnosis, privacy, and the erosion of the patient–clinician relationship [23], that comfort is conditional on physician supervision of the final decision [24,25], and that trust is lowest precisely for surgical applications [26]. Experimental work shows that acceptance of AI-based care rises when physicians endorse and explain the system [27,28], and that patients react negatively when AI use is not disclosed or when AI and clinician recommendations conflict [29,30]. A recent multinational hospital survey spanning 43 countries confirmed predominantly favorable views combined with a marked preference for explainable, physician-supervised AI [31]. Within surgery specifically, patients presenting to a surgical clinic reported low familiarity with and limited trust in AI involvement in their care [32], and users evaluating AI-enabled decision aids valued them for shared decision-making rather than autonomous decision-making [33]. Vignette-based population experiments identify system reliability and transparency as the leading drivers of support [34], and AI familiarity, education, and health literacy recur as determinants of acceptance [35,36].

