### 1.6. Objectives and Hypotheses

The primary objective is to evaluate the attitudes of Romanian adults recruited online—acceptability, trust, risk perception, and responsibility attribution—toward four progressive scenarios of AI implementation in facial reconstructive surgery. The secondary objectives are (i) to analyze the moderating effect of AI familiarity on acceptability across autonomy levels; (ii) to investigate how responsibility attribution (surgeon, hospital, AI developer, unavoidable medical uncertainty) varies across scenarios; (iii) to explore the moral–legal distinction in responsibility attribution; (iv) to identify the preferred model of AI implementation in facial reconstructive surgery; and (v) to quantify the influence of presentation sequence on all primary outcomes and to estimate the autonomy effect adjusted for serial position.

Four hypotheses will be tested. H1. Acceptability and trust decrease significantly as the level of AI autonomy in the surgical decision increases. H2. Perceived risk increases as human control over the decision process decreases. H3. Responsibility attribution shifts progressively from the surgeon toward the AI developer as algorithmic autonomy increases. H4. Prior familiarity with AI moderates the relationship between implementation scenario and acceptability, such that participants familiar with AI show a smaller decline in acceptability for high-autonomy scenarios; H4 is treated as partially exploratory, given the power constraints described in Section 2.5. H1–H3 fix the expected direction but not the functional form: each is tested by an omnibus effect of autonomy level followed by the full set of orthogonal polynomial contrasts, so that threshold-like or otherwise non-monotonic patterns are detected rather than forced into a linear trajectory (Section 2.9.1). A design-validation hypothesis is tested alongside them, namely that responses do not depend on the sequence in which the scenarios were presented; it is evaluated as the scenario × sequence interaction, and a non-null result is treated as evidence of order dependence to be reported and adjusted for, not as a substantive finding about autonomy.

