Several limitations are accepted by design and will be declared in the results article. First, the sample is a self-selected online convenience sample: results describe Romanian adults active in digital environments—likely younger and more educated than the general population—and do not support national generalization; the sample structure will be reported against National Institute of Statistics reference data. Second, the vignettes are hypothetical, and the distance between a vignette judgment and a decision taken in a consulting room is not merely one of degree. Participants evaluate a scenario in which they are not injured, not in pain, not facing a scheduled operation, and not choosing between real surgeons. They bear no consequences for the judgment they record, receive no counseling, and cannot ask questions. Above all, they are not exposed to the most influential element of real surgical decision-making: a conversation with the clinician who would operate, whose endorsement and explanation are known to shift acceptance of AI-supported care substantially [27,28]. Stated acceptability under these conditions is best read as a measure of prior disposition toward a described scenario rather than as a prediction of consent behavior. The ordering of the scenarios is likely to be more robust than the absolute levels, which could be lower than those a counseled patient would report or higher if hypothetical risk is discounted. This is a standard limitation of vignette methodology [61,62], and the remedies lie outside the present design: replication among patients actually scheduled for facial reconstructive surgery, and ultimately observation of consent decisions where such systems are in use. Third, presentation sequence is counterbalanced but not thereby rendered irrelevant. The Williams square balances serial position and first-order carry-over, so that the autonomy effect is estimable free of both, but no four-sequence design balances higher-order carry-over—a participant’s evaluation of the third scenario being shaped jointly by the first two—and contrast effects that depend on which scenario was seen immediately before therefore remain possible. The scenario × sequence interaction, the position-adjusted model, and the difficulty covariate bound the magnitude of what remains; they do not remove it, and a large residual would warrant a between-subjects replication in which each participant evaluates a single scenario. Fourth, demand and contrast effects are inherent to within-subjects designs: seeing all scenarios, participants may infer the study objective and exaggerate differentiation between scenarios; comparisons remain internally valid, but absolute difference magnitudes warrant caution. Fifth, all measures share a common method and a single measurement occasion, in a rapidly evolving attitude domain [38]. Sixth, the survey platform does not record completion time, so quality control relies on embedded checks rather than temporal filters [69]. Seventh, the demographic and familiarity subgroups formed within a convenience sample of 300 will differ substantially in size, and several will be small; the minimum-cell rule of Section 2.9.2, and the requirement that subgroup differences be inferred only from formal interaction terms, are intended to forestall the familiar error of asserting a difference from a significant effect in the larger subgroup together with a non-significant one in the smaller. None of these limitations is unusual for online vignette experiments, and declaring them in advance is intended to keep the eventual findings interpretable at their proper scope.

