## 5. Conclusions

This protocol specifies, in advance of any data collection, the design, measurement structure, power justification, quality-control procedures, and complete analysis plan for a counterbalanced within-subjects vignette experiment on the acceptability of progressively autonomous AI in facial reconstructive surgery among Romanian adults. These decisions are fixed a priori and bound through pilot validation and OSF pre-registration, and the presentation sequence is counterbalanced so that the autonomy gradient is separable from the order in which the vignettes are read. The study is therefore designed to yield interpretable, reproducible evidence on three questions: where public acceptance of surgical AI erodes along the assistance-to-autonomy continuum; how responsibility for AI-involved errors is assigned across surgeons, institutions, and developers; and which implementation configurations the Romanian public regards as acceptable entry points for AI in facial reconstructive surgery.

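### Section 2.4 wrongly says that scenario comparisons do not depend on who is recruited; the design protects their internal validity, not their size, and the conclusions about the Romanian public should be narrowed to match.

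*Protocol article*

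**What the plan says.** **Section 2.4.** Recruitment runs through social networks, forums, professional groups and "through the mailing lists of higher-education institutions". The protocol is open about the result: "The resulting sample is a non-random convenience sample". It disclaims national representativeness and promises to report the sample against National Institute of Statistics data. It then exempts the between-scenario comparisons, which it calls the primary objective, from this limitation: all participants rate all scenarios, "so that comparisons across autonomy levels do not depend on sample composition or recruitment method".

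**Section 1.6.** The primary objective concerns Romanian adults recruited online. H4 predicts that "participants familiar with AI show a smaller decline in acceptability for high-autonomy scenarios".

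**Sections 2.9.1, 2.9.2 and 3.** The plan fixes seven moderators, among them AI familiarity, education and age. It tests a random slope for the linear autonomy contrast, and Section 3 declines to assume that all participants share one pattern.

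**Section 4, limitations.** The results describe digitally active adults, "likely younger and more educated than the general population", and do not support generalization to the nation.

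**Sections 3, 4 and 5, conclusions.** The end of Section 3 promises to identify configurations acceptable to the public in Romania. The third contribution listed in Section 4 calls the data general-population data. Section 5 lists among the questions to be answered "which implementation configurations the Romanian public regards as acceptable entry points for AI in facial reconstructive surgery".

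**The concern.** The Section 2.4 sentence treats two properties as one. Comparing each person with themselves removes between-person differences in level, so the contrast is not confounded by who happened to answer. It does not make the contrast the same in everyone. Where people differ in how much they react to autonomy, the average reaction depends on which people are averaged.

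The protocol expects such differences and expects its sample to be skewed on variables tied to them. Section 1.2 notes that "AI familiarity, education, and health literacy recur as determinants of acceptance", and recruitment draws on online groups and universities.

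The direction of H1–H3 within the sample is not at stake. What is exposed is the size of the gradient, the step at which acceptance breaks, and any statement about which configurations the public would accept. A reader of Section 2.4 is told that the convenience sample does not touch these comparisons, and then meets conclusions worded for the Romanian public.

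**Working it through.** **1. The plan's own figures reproduce.** All at two-sided α = 0.05 and power 0.80 (Section 2.5, Table 2).
- Primary repeated-measures ANOVA: noncentral F with df 3 and 3(N − 1), noncentrality λ = f² × N × 4/(1 − ρ). For f = 0.25 and 0.10 this gives N = 24 and 138 at ρ = 0.50, and 32 and 193 at ρ = 0.30, as stated. Power at N = 300 for f = 0.10 is 0.991 and 0.949 (stated 0.99 and 0.95).
- Scenario × familiarity interaction: noncentral F with df 3 and N − 4, λ = f² × N. The minimum detectable f² at N = 300 is 0.0368 (stated 0.037), and f² = 0.02 needs N = 550 (stated ≈ 550).
- Pairwise comparisons at N = 300: dz = 0.162 uncorrected and 0.202 at α = 0.05/6 (stated 0.16 and 0.20).

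No power figure is wrong. The fault lies in the inference drawn from the design.

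**2. Why the mean contrast depends on the mix.** Let D be one person's difference between two scenarios and F that person's familiarity, with

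D = δ + β(F − μ) + error,

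where μ is mean familiarity in the wider population and δ the mean contrast there. Averaged over a sample with mean familiarity m, the expected contrast is δ + β(m − μ). Any person-level constant has already cancelled in D; that is what the within-subjects design achieves. The term β(m − μ) remains and vanishes only if β = 0 or m = μ. H4 says that β ≠ 0 for acceptability. The limitations in Section 4 give reason to doubt m = μ.

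**3. Size, as an illustration.** In units of the SD of D, the shift is r × s, where r is the correlation of D with F and s = (m − μ)/SD(F). If all the moderation falls on one contrast, r = √(f²/(1 + f²)):
- f² = 0.02: r = √(0.02/1.02) = 0.140
- f² = 0.037: r = √(0.037/1.037) = 0.189

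| Assumed gap s | Shift at f² = 0.02 | Shift at f² = 0.037 |
|---|---|---|
| 0.25 SD | 0.140 × 0.25 = 0.035 | 0.189 × 0.25 = 0.047 |
| 0.5 SD | 0.140 × 0.5 = 0.070 | 0.189 × 0.5 = 0.094 |
| 1 SD | 0.140 × 1 = 0.140 | 0.189 × 1 = 0.189 |

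The documents give no value for s; 0.25 to 1 SD is an assumed range. For scale, Section 2.9.1 sets the smallest effect of interest at dz = 0.20.

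**4. The study cannot clear the sentence with its own data.** At N = 300, power for f² = 0.02 is 0.51, and Section 2.5 says that a non-significant H4 will not be read as absence of moderation.

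**The case against.** The strongest reply is that Section 2.4 makes an internal-validity claim in loose words. The sentence opens with validity, the disclaimer of representativeness stands directly before it, and Section 1.6 sets the target as Romanian adults recruited online. For that target, a digitally active sample is scope and not bias. Section 4 repeats the limit. The plan also studies heterogeneity directly: H4, seven moderators reported whether significant or not, a random slope and trajectory classes.

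Much of this stands, and it rules out several stronger readings:
- **That H1–H3 are invalid or biased.** The tests are sound for the people sampled, and H4 predicts a smaller decline, not a reversed one. Section 4 itself expects the ordering to be more robust than absolute levels.
- **That every outcome is predicted to shift.** H4 concerns acceptability only. For trust, perceived risk and responsibility, the planned moderator and random-slope analyses allow for heterogeneity but do not predict it.
- **That a shift near dz = 0.19 is to be expected.** f² = 0.037 is a minimum detectable effect, placed here on one contrast, and the 1 SD gap is assumed. The 0.20 bound was set for equivalence tests, not as a tolerance for bias.

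The reply does not rescue the clause itself, which names sample composition and recruitment method and denies any dependence on either. Nor does it explain the public-level wording in Sections 3, 4 and 5.

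**Conclusion.** The Section 2.4 statement is wrong as written. It would hold only if no characteristic that differs between the sample and the wider population changed the scenario effect. The protocol predicts such a change for acceptability and leaves it open for the other outcomes. The general-population and Romanian-public wording in Sections 3, 4 and 5 also conflicts with the target in Section 1.6 and the limits in Section 4.

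The size is uncertain: dz of about 0.035 to 0.19 on a single contrast, from small to nearly the plan's smallest effect of interest. This rests on linear moderation by familiarity, f² between 0.02 and 0.037 carried by one contrast, and a familiarity gap of 0.25 to 1 SD that the documents do not supply. No primary test, sample size or power figure needs to change. What changes is what the results may be said to show.

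**What to change.** 1. **Section 2.4.** Replace the clause with a statement that the within-subjects design protects the internal validity of the scenario comparisons in this sample, but that their size may depend on sample composition and recruitment.
2. **Sections 3, 4 and 5.** Limit the closing sentence of Section 3, the third contribution in Section 4 and the last question in Section 5 to Romanian adults recruited online, in line with Section 1.6 and the limitations. Make this unconditional.
3. **Optional, labeled exploratory.** Standardize the scenario contrasts to National Institute of Statistics margins for age, education and residence environment (D2, D3, D6), shown beside the unstandardized results. State a rule for D6 records with a declined answer, which Section 2.7 permits. Leave out D1, which Section 2.10 reserves for describing the sample. Say plainly that the analysis widens intervals and cannot correct for familiarity. Agreement between the two sets of results would not justify national conclusions from a self-selected sample.

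Items 1 and 2 cost a few sentences. Item 3 costs one re-analysis of items already collected, using a reference source already planned. Data collection has not started and pre-registration is still to come (Section 2.12), so all of this can be settled beforehand.
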